### 7.3 LOST TO FOLLOW-UP

The study team will consider caregiver/child dyad participants lost to follow-up if they do not complete the final [study assessment](#). Those who do not complete any [clinical assessments](#) (RAMP Reports or paper assessments)

will still be included if they complete the final [study assessment](#) as this is an intention to treat analysis. To minimize the number of participants lost to follow-up, the study team will contact participants approximately 1 week, 4 weeks, and 2 months after consent to ensure there are no technology issues.

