The entire timeline will span 17 months with three phases. In the first phase of the study, the providers from the participating practices will receive ADHD Best Practices education and training in the portal use, and will be asked to provide informed consent. A member of the clinic staff (nurse, medical assistant or practice manager) will be identified as site champion. The site champion will facilitate communication between the site study team and the clinic staff. The second phase of the study will focus on child/caregiver and provider utilization. Providers will identify patients with a diagnosis of ADHD who are being started on stimulant medication to be contacted by study staff for enrollment. Research coordinators will discuss the study, perform eligibility screening and obtain consent (if deemed eligible by PI). The consented caregiver/child dyads will be randomized to intervention (requests to submit the RAMP Reports for 3 months) or control (usual care with attention control) groups. Families will be approached until 36 caregiver/child dyads are enrolled (only one child in a family may be enrolled). Each practice will have 6 weeks to enroll 9 participants. After the 6 weeks, practices with low enrollment will receive additional supports. Each week, progress to target will be evaluated to determine if any practice needs additional resources. If multiple practices do not meet enrollment goals, the study team may consider relaxing exclusion/widening inclusion criteria (ex. include patients undergoing re-titration, widen age criteria) and/or opening enrollment. Enrollment will be paused for 3 months from the last month of school to the start of the new school year (beginning of May to end of July). This will decrease the burden on practices and study staff during the time of the year with the fewest number of ADHD diagnoses. Once enrolled, caregiver/child participants will be randomized to either the intervention or control group and followed for approximately 3 months. Participants randomized to the intervention group will submit RAMP reports weekly for 4 weeks and then monthly for 2 months. Participants randomized to the control group will receive digital education handouts at the same frequency as the RAMP reports in the intervention arm. Research coordinators will periodically review the child participant's EMR and mark how many paper symptom assessments are returned while enrolled on the study for both groups. Research coordinators will also access the RAMP platform to log RAMP reports returned by caregivers/teachers, RAMP reports reviewed by providers, and provider survey results. All caregiver participants will complete a 90-day Vanderbilt Assessment as a retention measure (see section 1.2.1 for more details). This phase will continue until all 36 participants have completed their 3-month study period. In the third phase, the above endpoints will be calculated, the full-scale trial will be designed, and the findings presented in a manuscript.

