## 8 STUDY ASSESSMENTS AND PROCEDURES

### 8.1 EFFICACY ASSESSMENTS

#### PRIMARY OUTCOME MEASURES

##### **Objective 1 – Evaluate completion of clinical assessments by caregivers and teachers.**

The number of completed clinical assessments (either paper assessments [control] or RAMP Reports [intervention] that are returned to providers during the 3-month study period will be counted. Each RAMP Report will be documented in the RAMP platform including a timestamp of submission. Throughout the study period, the research coordinators will facilitate recruitment, randomization, support retention, and perform chart abstraction.

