### 9.3 POPULATIONS FOR ANALYSES

To evaluate completion of clinical assessments and provider acceptability, the study will have two analysis populations:

1. Intention-to-treat (ITT) population – This population will include all participants randomized into the study.
2. Per-protocol (PP) population – This population will include all participants in the ITT population who completed the final **study assessment**.

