### 9.4.2 ANALYSIS OF THE PRIMARY ENDPOINT(S)

Determining the utilization of **clinical assessments** (paper assessments in control group and RAMP Reports in intervention group) in rural primary care clinics will be a key parameter necessary for conducting a future main trial. Utilization will be determined by assessing the numbers of completed caregiver reports and teacher reports in each of the groups (intervention and control). Counted reports include any **clinical assessment** including paper assessment or RAMP Report that is submitted to a provider but not the midpoint and endpoint **study assessment** that will be for study purposes only. Any paper assessments submitted for intervention group participants will be counted separately from the RAMP reports and a sensitivity analysis will be performed to gain insight into that data. Data analysis will report mean, standard deviation, median, and interquartile range for each utilization measure overall and stratified by intervention group. Additionally, we will develop a Poisson regression model to compare the number of returned structured reports across the groups. We will report the expected mean number of reports in each group along with their difference with 95% confidence interval (CI).

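### Section 7.3 makes inclusion of zero-report dyads depend on the Day 90 form and calls this intention to treat, which conflicts with the ITT definition in Section 9.3 and would inflate each arm's mean utilization

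*Protocol*

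**What the plan says.** All of the following is current protocol text.

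- **Section 7.3, loss to follow-up.** "The study team will consider caregiver/child dyad participants lost to follow-up if they do not complete the final" study assessment. The next sentence takes up dyads with no clinical assessment at all (no RAMP Report and no paper form). They "will still be included if they complete the final" study assessment, and the reason given is that the analysis is by intention to treat.
- **Section 9.3, ITT.** "This population will include all participants randomized into the study". No condition is attached.
- **Section 9.3, per-protocol.** "This population will include all participants in the ITT population who completed the final" study assessment.
- **Section 8.1, primary outcome.** Clinical assessments "that are returned to providers during the 3-month study period will be counted". For the intervention arm, "Each RAMP Report will be documented in the RAMP platform including a timestamp of submission".
- **Section 4.1, paper forms.** Research coordinators go through the medical record periodically and "mark how many paper symptom assessments are returned while enrolled on the study for both groups".
- **Section 9.4.2.** Study assessments are left out of the count because they are forms "that will be for study purposes only". The same section calls utilization a key parameter for the main trial. It plans a Poisson model and reports the expected mean in each group and their difference with a 95% confidence interval.

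**The concern.** Two sections use the name intention to treat for two different sets. Section 7.3 attaches to it a condition, return of the final form, that Section 9.3 reserves for the per-protocol population. An analyst who follows 7.3 and one who follows 9.3 would build different primary datasets, and a SAP that agrees with either section contradicts the other.

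The condition is also unnecessary. The outcome is a count of forms that reach the provider, so zero is a valid value, and it is seen in the platform log and the chart without the Day 90 form. Dropping a dyad because it has no reports and no Day 90 form is selection on the outcome: it removes the least engaged families. What is at stake is the mean number of assessments per dyad in each arm, which Sections 3 and 9.4.2 want for planning the full-scale trial.

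**Working it through.** **Plan's own figure.** The protocol states no number on this point. The only precision statement, in Section 9.2 (25% recruitment and 50% adherence, each within 12–14 points at 90% confidence, n=36), reproduces: 1.645 × √(0.25×0.75/36) = 11.9 points and 1.645 × √(0.5×0.5/36) = 13.7 points. The present point does not depend on it.

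**Step 1: who is included under each section.**

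| Dyad | ITT by 9.3 | 7.3 read naturally | Per-protocol by 9.3 |
|---|---|---|---|
| No reports, Day 90 form returned | in | in | in |
| No reports, Day 90 form missing | in | out | out |
| At least one report, Day 90 form missing | in | not addressed | out |

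The second row is the contradiction. The third row is a gap: 7.3 labels such dyads lost to follow-up but does not say whether they are analysed.

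**Step 2: effect on an arm mean.** Inputs are 18 dyads per arm (Section 9.2) and k zero-count dyads dropped (assumed). If T is the arm's total number of reports, the ITT mean is T/18. The dropped dyads add nothing to T, so the 7.3 mean is T/(18−k). The ratio is 18/(18−k).

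| k | Inflation of the arm mean |
|---|---|
| 1 | 18/17 = 1.06 |
| 2 | 18/16 = 1.13 |
| 3 | 18/15 = 1.20 |
| 6 | 18/12 = 1.50 |
| 9 | 18/9 = 2.00 |

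Over an assumed range of 2 to 9 zero-report dyads per arm, with 25% to 100% of them missing the Day 90 form, the inflation runs from 1.03 (2 × 0.25 = 0.5 dropped on average) to 2.00 (all 9 dropped).

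**Step 3: effect on the difference in means, the contrast named in Section 9.4.2.** From the protocol: (4+2) requests × 2 reporters = 12 possible RAMP Reports, and an expected return of 52.7%, so 12 × 0.527 = 6.32. Assumed: control counts are Poisson with mean 1 (share of zeros e^−1 = 0.368), a share s of RAMP dyads returns nothing and the rest average 6.32, and a share m of zero-report dyads misses Day 90 in both arms. Under 7.3 the control mean is 1/(1 − 0.368m) and the RAMP mean is 6.32(1−s)/(1 − sm).

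| s | m | ITT difference | 7.3 difference |
|---|---|---|---|
| 0 | 1.0 | 6.32 − 1.00 = 5.32 | 6.32 − 1.58 = 4.74 |
| 0.1 | 0.5 | 5.69 − 1.00 = 4.69 | 5.99 − 1.23 = 4.77 |
| 0.3 | 1.0 | 4.43 − 1.00 = 3.43 | 6.32 − 1.58 = 4.74 |

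The difference falls, hardly moves or rises, according to where the zeros lie.

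**Step 4: a more dispersed scenario.** Assumed: RAMP counts beta-binomial (12 requests, 0.527, within-dyad correlation 0.4, 9% zeros); control negative binomial with mean 1 and 50% zeros; Day 90 form returned by 30%, 50% or 70% of zero-report dyads. In 20,000 simulated trials the 7.3 rule gives control means of 1.54, 1.33 and 1.18, which agree with 1/(1 − 0.5(1−r)) for return share r, and RAMP means of 6.77, 6.63 and 6.51. The differences are 5.23, 5.30 and 5.33, against 5.32 with everyone kept. So the control mean is overstated by 18% to 54% while the difference moves by at most about 2%.

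**The case against.** **The text says if, not only if, and Section 9.3 governs populations.** The sentence could mean merely that a dyad with no reports does not count as lost to follow-up provided it returns the Day 90 form. If 9.3 prevails, no zero is removed. This is a fair reading of intent, and it is why the point is a conflict to reconcile and not a settled rule to discard data. But stating completion as the condition, directly after labelling non-completers lost to follow-up, leads most readers to the restrictive reading.

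**The treatment comparison need not be badly biased.** A reader might infer that the rule distorts the treatment effect in a known direction, for example because zeros are commoner in control. In the Step 4 scenario the ratio of means does fall from 6.3 to between 4.4 and 5.5. The documents do not support that as a general conclusion. Section 9.4.2 reports the difference, which in the same scenario barely changes, and Step 3 shows it can go either way. Loss could also fall more on the RAMP arm, since Section 7.2 withdraws caregivers who confirm that they want the texts stopped, and RAMP texts go only to that arm.

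**Few dyads may be affected.** Section 5.5.3 pays $100 for the Day 90 form and allows up to two follow-up calls, so k may be small. This stands; every value of k used here is an assumption.

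**The count is not complete for everyone.** It would be too strong to say that every randomized dyad has a full three-month count. Section 7.2 ends platform access at withdrawal, and Section 4.1 counts paper forms only while a dyad is enrolled. Counts after withdrawal are truncated. That is a reason to say how they are handled, and it does not justify the 7.3 condition.

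**The per-protocol label.** One might also object to calling Day 90 completers per-protocol. The Day 90 assessment is a scheduled activity and 9.3 defines the set openly, so this is naming only.

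**Conclusion.** The contradiction between Sections 7.3 and 9.3 is real. Followed as naturally read, 7.3 removes observable zeros from an analysis it calls intention to treat, and each affected arm's mean utilization is inflated by exactly 18/(18−k): modest if one dyad is lost (6%), material if three (20%) or six (50%) are. The factor is arithmetic and assumes 18 dyads per arm; k is unknown.

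The harm lies in the per-arm planning rates. No direction or size can be claimed for the between-arm difference. Zero-report dyads who return the Day 90 form stay in under either section, so it would also be wrong to say that 7.3 removes all non-users.

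**What to change.** - **Section 7.3.** Replace the conditional sentence with one stating that every randomized dyad is in the ITT analysis in its assigned arm with its observed count of clinical assessments, zero if none was returned, whether or not the final study assessment is completed. This also settles dyads who have some reports but no Day 90 form.
- **Withdrawals.** Add that a withdrawn dyad contributes the count observed up to withdrawal, and that the report will acknowledge these counts as truncated and give their number by arm.
- **Day 90 form.** Use it only as the retention marker and to define the per-protocol set in Section 9.3, with that set analysed as a sensitivity analysis. The set needs no new name.
- **SAP.** Carry the same wording into the SAP before data lock.

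The cost is a few sentences in an amendment. No new data, visits or participants are needed. Where zero-report dyads without a Day 90 form exist, the reported arm means will be lower than under 7.3, which is the correct result for planning.

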## 8 STUDY ASSESSMENTS AND PROCEDURES

### 8.1 EFFICACY ASSESSMENTS

#### PRIMARY OUTCOME MEASURES

##### **Objective 1 – Evaluate completion of clinical assessments by caregivers and teachers.**

The number of completed clinical assessments (either paper assessments [control] or RAMP Reports [intervention] that are returned to providers during the 3-month study period will be counted. Each RAMP Report will be documented in the RAMP platform including a timestamp of submission. Throughout the study period, the research coordinators will facilitate recruitment, randomization, support retention, and perform chart abstraction.

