- Evaluate provider utilization of the RAMP platform in everyday practice and management of children early in the treatment course of ADHD

Participants will be recruited from four practices with high rural and/or underserved populations from two ISPCTN awardee sites. Participation will be required by all providers who manage ADHD at the four practices. Prior to the start of caregiver/child recruitment, all providers at the clinics will receive ADHD Best Practice education consistent with the 2019 American Academy of Pediatrics (AAP) clinical practice guidelines for diagnosis and management of children with ADHD. Families with children aged 5-11 years with a diagnosis of ADHD who are initiating medication for the first time (either new diagnosis or prior diagnosis

without stimulant treatment) or have not received stimulants for the last 3 months will be approached to participate. Families will be approached until 36 caregiver/child dyads are enrolled (only one child in a family may be enrolled). Those enrolled will be randomized 1:1 to either the intervention group or control group. The intervention group will be enrolled in the RAMP, with prompts to provide frequent reports including ADHD symptoms. The control group will provide ADHD symptom reports through paper forms (usual care), on a provider determined schedule. While we will recommend that a Vanderbilt Assessment be used, providers may use a symptom screener of their choice for usual care. The control group will also receive digital education handouts about age-appropriate pediatric health topics (e.g., general health, exercise, digital media, sleep) in children on the same schedule as the RAMP requests are sent to caregivers and teachers for participants in the intervention group. Each group will have provider-directed medication management of ADHD (usual care).

The outcomes examined in the pilot include feasibility and acceptability of the RAMP to caregivers, teachers and providers. Participant utilization of the RAMP will be measured. Provider engagement with the RAMP will be explored using data review logs.

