Providers will receive ADHD Best Practices education at the start of the study including recommended use of the Vanderbilt Assessment and appropriate follow-up as well as how to utilize the RAMP platform. The project is not focused on the effect of provider training, as these are not new guidelines, but rather addresses other potential barriers that are unique to rural settings. After enrollment of caregiver/child participant dyads, providers will be alerted by their preferred means (text or email) when new RAMP Reports are available for review. Following RAMP report review, the provider will answer a brief 2-question, survey regarding their response to the report. Providers will be able to view the individual as well as prior reports in their dashboard view.

Research coordinators will monitor caregiver and teacher activity, including providing RAMP Report responses and provider activity in reviewing responses, and following up with caregivers and providers as outlined in the retention plan to determine if there have been gaps in or a lack of engagement.

The control group caregiver participants will receive digital education handouts about age-appropriate general pediatric health topics (e.g., exercise, digital media, sleep) weekly for 4 weeks then monthly for 2 months (the same interval as RAMP requests in the intervention group).

- |                                                                                                                                                                                                                                                                      |
|----------------------------------------------------------------------------------------------------------------------------------------------------------------------------------------------------------------------------------------------------------------------|
| 

• Clinical assessment: any paper assessment or RAMP Report reviewed by health care provider

• Study assessment: Vanderbilt Assessment at Day 90, reviewed only by study team

 |
|----------------------------------------------------------------------------------------------------------------------------------------------------------------------------------------------------------------------------------------------------------------------|

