| Evaluate completion of clinical assessments by caregivers and teachers. | Number of completed caregiver and teacher clinical assessments (RAMP Report or paper assessment) that are returned to provider | The level of ongoing caregiver and teacher engagement in each arm will be important for planning a full-scale trial. Absolute number will be used as this is what has been shown to improve ADHD symptom control.  Increasing communication between caregivers and providers is important in enhancing the care of individuals with ADHD and literature in this area in rural settings is lacking. |
| Secondary                                                                             |                                                                                                                                       |                                                                                                                                                                                                                                                                                                                                                                                                                 |
| Evaluate provider acceptability of the RAMP through utilization measures.      | Proportion of provider review surveys with at least one available RAMP Report where review is documented                              | Because improvement in care requires bi-directional communication, the review of newly available reports by the provider will be important to measure. While we anticipate that providers will find accessing this information easy and helpful, it may be difficult to incorporate into usual workflow.                                                                                                        |

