**Rationale for randomizing at the patient level:** RAMP is an automated communication tool designed to eliminate the work burden for providers of requesting and receiving ADHD symptom data from participants. Thus, providers will not be able to reproduce the RAMP intervention for control participants. However, this is an unblinded pilot, and we do not expect providers to change their patient counseling based on participant condition allocation. Therefore, providers should not be confused by receiving RAMP Reports for some study participants (in the experimental condition) and not receiving RAMP Reports for others (in the control). While providers may increase the frequency of their self-initiated outreach to control participants because of the frequency with which they receive RAMP Reports for experimental condition participants, this bias would likely result in more Type II (false-negative) errors for determining intervention effectiveness, which is preferable to Type I (false-positive) errors.

**Rationale for using digital education handouts:** The digital education handouts will be sent via email to the control group and will serve as an attention control. They will consist of information regarding a general pediatric health topic and will be emailed at intervals matching the RAMP requests in the intervention group.

**Rationale for the schedule of [study assessments](#):** The study team will collect the diagnostic assessment from both the intervention and control groups at 0 months (enrollment), as well as a [study assessment](#) (not shared

with provider and clearly marked as such) at Day 90 (-30/+15) — the study final participant follow-up. The diagnostic assessments will be on paper and will be obtained from the diagnosing provider with caregiver permission. The subsequent [study assessments](#) will be obtained either on paper or electronically (caregiver choice). These [study assessments](#) will serve as markers of retention. Caregiver participant incentives will be based on return of these [study assessments](#).

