**Practice selection:** A total of 4 pediatric or family practice locations will be selected from two ISPCTN awardee sites, with each site recruiting at least 1 practice location for participation. Practices should care for at least 700 patients aged 5-11 years and should regularly diagnose and manage pediatric ADHD. With 700 children and a pediatric ADHD prevalence of 11%, we expect on average 77 children with ADHD across the inclusion age group, many of whom will be initiating stimulant medication for the first time, considering median age of onset is 6 years. Practices will be designated as rural if they are at least 30 minutes travel distance from a pediatric academic medical center (similar to prior studies) and are located in a city with less than 50,000 people. Practices will be designated underserved if at least 40% of its pediatric patient visits are covered by Medicaid. Practices must use an EMR as this pilot aims to use typical practices in preparation of the full-scale trial. 2019 National Electronic Health Records Survey found that 89.9% of office-based physicians were using an EMR.

Use of electronic prescribing is preferred but not required. Practices must also be willing (and preferably experienced) in using the Vanderbilt Assessment as their primary tool for ADHD diagnosis and management. Providers must agree in concept to participate in the ADHD Best Practice education, as well as instruction on using the RAMP platform and will provide informed consent (see provider eligibility below). Interested ISPCTN sites will assess eligible practices and choose the best fit. Locations will be submitted by interested ISPCTN sites and will be evaluated by the Data Coordinating Operations Center (DCOC). Selection will occur and ISPCTN sites will be notified.

**Provider eligibility:** Providers of the eligible practices will be included if:

- they manage ADHD care in patients age 5-11 years
- provide informed consent
- agree to use the RAMP platform if they care for patients randomized to use it
- agree to provide information to potential participants about the study and contact the research coordinator if interested

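### The counting and capture rule recognises only paper forms and RAMP Reports, so a structured report that usual care returns by another electronic route would be neither counted nor recorded

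*Protocol*

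**What the plan says.** **The counted unit.** The box in Section 1.1 defines a clinical assessment as "any paper assessment or RAMP Report reviewed by health care provider". The primary endpoint in Sections 1.1 and 3 repeats the two formats: "RAMP Report or paper assessment) that are returned to provider". Section 8.1 ties each format to an arm: "either paper assessments [control] or RAMP Reports [intervention".

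**How reports are found.** Section 4.1 has coordinators review the EMR and mark the number of paper symptom assessments, in both groups, and log RAMP Reports from the platform. The first footnote to Section 1.3 limits what may be taken from chart and platform: whether the paper form or RAMP Report is present, when it was submitted, and whether a provider reviewed it.

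**How reports are analysed.** Section 9.4.2 first restates paper for control and RAMP Reports for intervention. It then counts any clinical assessment, "including paper assessment or RAMP Report that is submitted to a provider", and specifies a "Poisson regression model to compare the number of returned structured reports across the groups". Paper forms in the intervention arm are counted separately, with a sensitivity analysis.

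**What usual care looks like.** Section 1.1 states: "The control group will provide ADHD symptom reports through paper forms (usual care), on a provider determined schedule". It also leaves the choice of screener to the provider. Section 5.1 adds: "Practices must use an EMR as this pilot aims to use typical practices". Section 4.2 foresees that "providers may increase the frequency of their self-initiated outreach to control participants", and expects this to bias the comparison towards a false negative.

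**The concern.** The stated reason for the endpoint (Section 3) is that the absolute number of reports is what improves symptom control. That reason applies to a Vanderbilt form completed in a patient portal as much as to one on paper. The analysis section also speaks of structured reports, a term not bound to a format. Yet the definition, endpoint, outcome measure, coordinator instruction and abstraction limit all stop at two formats. Electronic reporting is thus credited only when it passes through the intervention's own platform, in a comparison that is not blinded.

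The capture rule makes this more than loose wording. If a portal or e-mailed form is outside what coordinators may abstract, it will not be in the database, and no later SAP can restore it.

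Two things are at stake. The pilot is meant to supply the utilization of each arm for the main trial, and a usual-care rate that leaves out one channel would be too low. The argument in Section 4.2 that extra outreach to controls can only be conservative holds only so far as the reports it produces are captured.

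**Working it through.** **No figure in the plan to reproduce on this point.** The protocol gives no expected control count and no share of non-paper reports. The precision statement in Section 9.2 does reproduce (1.645 × √(0.25 × 0.75/36) = 11.9 points; 1.645 × √(0.5 × 0.5/36) = 13.7 points, against 12 to 14 stated), but it does not bear on the counting rule.

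**Does the word including in Section 9.4.2 reopen the rule?** It qualifies the term clinical assessment, which Section 1.1 has already defined as one of two formats, and the opening sentence of 9.4.2 again limits control to paper. Even on the open reading, the data would be missing, because Sections 1.3 and 4.1 provide only for paper forms and RAMP Reports.

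**Inputs.**
- RAMP requests per child: (4 weekly + 2 monthly) × 2 reporters = 12 (Section 6.1.1).
- Expected RAMP return rate: 52.7% (Section 9.2), applied here to both reporters. Mean RAMP Reports = 12 × 0.527 = 6.32.
- True control mean m_C: not given; assumed 0.6 to 3.0.
- Share of control reports arriving by a route that is neither paper nor RAMP, u: not given; assumed 0 to 30%.
- Corresponding share lost in the intervention arm, v: not given; set to 0 in the table.

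**Formulas.** With true means m_I and m_C:
- observed control mean = m_C × (1 − u)
- observed ratio = (m_I/m_C) × (1 − v)/(1 − u)
- observed difference = (m_I − m_C) + u × m_C − v × m_I

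With v = 0 the ratio is multiplied by 1/(1 − u): 1/0.9 = 1.11, 1/0.8 = 1.25, 1/0.7 = 1.43.

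**Results with m_I = 6.32 and v = 0 (ratio; difference).**

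| m_C | u = 0 | u = 10% | u = 20% | u = 30% |
|---|---|---|---|---|
| 0.6 | 10.5; 5.72 | 11.7; 5.78 | 13.2; 5.84 | 15.1; 5.90 |
| 1.2 | 5.3; 5.12 | 5.9; 5.24 | 6.6; 5.36 | 7.5; 5.48 |
| 2.0 | 3.2; 4.32 | 3.5; 4.52 | 4.0; 4.72 | 4.5; 4.92 |
| 3.0 | 2.1; 3.32 | 2.3; 3.62 | 2.6; 3.92 | 3.0; 4.22 |

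The difference, which Section 9.4.2 says will be reported with its confidence interval, moves by u × m_C: from 0.06 (0.1 × 0.6) to 0.9 (0.3 × 3.0) reports per child.

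**Offset.** If v = u, the ratio is unbiased. If u = 20% and v = 5%, the factor is 0.95/0.80 = 1.19 instead of 1.25.

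**Effect on the test in the least favourable case.** Suppose the arms truly returned equal numbers. With 18 per arm, Poisson counts without overdispersion and v = 0, simulation puts the chance of a nominally significant result favouring RAMP at about 2.5% for u = 0, 6% to 12% for u = 10%, and 20% to 52% for u = 25%, for true means between 2.0 and 6.3. Equal arms are far from what the protocol expects, so this bounds the problem and does not predict it.

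**The case against.** The strongest reply is that paper is simply what usual care is. Section 1.1 says controls report on paper. Section 2.2 describes forms carried home or faxed, and says that rural practices may struggle with EMR-embedded tools. Section 6.2 speaks of the hardships of paper, and Section 10.1.1 has usual-care teachers returning paper forms. If that is complete, u = 0 and there is no bias. This stands, and it is why the size can only be given conditionally.

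Several stronger readings are tempting and are not supported.
- A reader might infer that the RAMP effect is inflated. Nothing in the protocol shows that portal or e-mailed reports occur at these practices. The same gap would also miss non-RAMP electronic reports in the intervention arm, so the net bias depends on the difference between arms.
- A reader might infer that provider outreach to controls goes uncounted. Outreach is not a report format, and any paper form it yields is counted.
- A reader might take the EMR requirement or the free choice of screener as evidence of electronic questionnaires. The first concerns the record system and the second the instrument; neither establishes a route.
- Faxed forms are, in Section 2.2, a way of returning the paper form, so nothing suggests they are excluded.

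It is also fair that the abstraction limit was not written as a counting rule. The version history records it as a central IRB contingency. It nevertheless fixes what coordinators may collect.

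What the reply does not answer is that the protocol describes usual care without guaranteeing it. Practices may qualify as underserved without being rural, providers may try to match the RAMP schedule for controls (Section 6.2), and no rule says what to do with a structured report that arrives off paper.

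**Conclusion.** The point holds as a gap in the counting and capture rule, not as a demonstrated bias. Sections 1.1, 1.3, 3, 4.1 and 8.1 recognise two formats; the rationale in Section 3 and the model in 9.4.2 concern structured reports as such. If a share u of control reports arrives by another electronic route and the intervention arm loses none, the control mean is understated by u and the ratio multiplied by 1.11, 1.25 or 1.43 at u = 10%, 20% or 30%. The absolute difference moves by 0.06 to 0.9 reports for assumed control means of 0.6 to 3.0. With u = 0 there is no effect, and an equivalent loss in the intervention arm reduces it. Neither u nor the control mean is in the protocol. The matter should be corrected because the reports, if they occur, would be lost to any later analysis, and because the remedy is cheap.

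**What to change.** Reconcile the definition and endpoint in Section 1.1, the abstraction footnote in 1.3, the endpoint in 3, the coordinator instruction in 4.1, the outcome measure in 8.1 and the counting rule in 9.4.2. In all of them, any structured ADHD symptom report completed by a caregiver or teacher and returned to the provider should count in the same way in both arms, whatever the route. The parenthesis in 7.3 should follow.

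Add the route of return (RAMP, paper including fax, EMR portal, e-mail, other) to the items that may be abstracted. Report the paper/RAMP-only count as a sensitivity analysis; it shows directly how much the rule matters, and if no other route is used the two counts coincide.

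Cost: one CRF field, slightly more time in a chart review already planned, and IRB approval of the revised footnote, since recording route goes beyond the present limit.
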